### Study population

Fourteen practice networks in two German federal states (Bavaria and North Rhine-Westphalia) are recruited for participation in the ARena project. For administrative reasons, the study will focus on patients insured by AOK health insurance, which are registered within a specific program for healthcare delivery (‘Besondere Versorgung’ as defined by German law § 140a SGB V a.F. bzw. § 140a Abs. 1. S. 2 Alt. 1 SGB V n.F). Compared to patients insured by other German health insurances, AOK-insured patients have somewhat lower income, less education, higher probability of migration background and lower self-reported health status [14]. On average, 35% of the population within the geographic reach of the participating practice networks in Bavaria are insured by AOK health insurance. At baseline, approximately 40,000 patients with AOK health insurance are registered in 193 participating ambulatory care practices in these 14 networks. In total, there are 304 eligible ambulatory care practices in these 14 networks. The patient population for the intervention arms will comprise patients who attended ambulatory practices for the following reasons: acute non-complicated infections of the respiratory tract (bronchitis, sinusitis, tonsillitis, otitis media), non-complicated cystitis and community-acquired pneumonia (CAP). The diagnoses will be based on physician-recorded ICD codes in administrative data, which are provided for reimbursement and lumped in 3-month periods.

### Inclusion criteria

In order to be able to fill in the data collection tools used within the process evaluation (e.g. questionnaires), all physicians, medical assistants, stakeholders and patients, participating in the patient survey, should have written and spoken German language skills and have to be 18 years of age or older. Additionally, written informed consent is a prerequisite for participation in the study.

#### Ambulatory practices and healthcare providers

Ambulatory practices need to be enrolled in one of the 14 participating practice networks in Bavaria and North Rhine-Westphalia to be eligible for participation. In addition, physicians need to participate in one of the following medical specialist groups: general practitioner (Facharzt für Allgemeinmedizin, GP), internists, gynaecologist, ENT specialist, urologist, pulmonary specialist or paediatrician (Additional file 2: Table S1). Out of these eligible ambulatory practices, physicians specialised in general practice or internal medicine and functioning as GP will be included in the outcome evaluation. All physicians, who participate in one of the intervention arms, will be invited to take part in the process evaluation. Additionally, GPs included in the outcome evaluation will have the opportunity to participate in focus group meetings.

Medical assistants employed at one of the eligible and participating ambulatory practices, which are allocated to intervention arm B, are eligible for study participation and will be invited to take part in the process evaluation, as well.

#### Patients

Eligible are patients with a diagnosis of an acute non-complicated infection of the respiratory tract (bronchitis, sinusitis, tonsillitis, otitis media), acute non-complicated cystitis or CAP who are insured by AOK health insurance in Bavaria or North Rhine-Westphalia. Eligible patients of ambulatory practices in intervention arm B, which are insured by the AOK health insurance in Bavaria, will be invited to participate in a patient survey.

### Exclusion criteria

No additional exclusion criteria for participants are defined. Patients, stakeholders, ambulatory practices and healthcare providers who do not fulfil the specific inclusion criteria in each part of the study (outcome evaluation, process evaluation and patient survey) will be excluded.

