### Recommended clinical practice

Recommendations for antibiotic prescribing are derived from several German high-quality, evidence-based clinical guidelines, most of which were developed by the German College of General Practitioners and Family Physicians (DEGAM) [2, 15]. All guidelines used are systematically developed, evidence- and/or consensus-based and conform with the quality standards for guidelines in Germany [16]. In short, they recommend restrained prescription of antibiotics, particularly in healthy patients with acute non-complicated symptoms. If antibiotics are used, recommended ones should be preferred instead of broad-spectrum antibiotics, like quinolones, for example.

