### Primary and secondary outcome measures

The primary as well as the secondary outcomes of the claims data based evaluation are defined and operationalized based on previous research in Germany [17]. Pseudonymized claims data (§§ 295, 300 SGB V) are used to construct different European Surveillance of Antimicrobial Consumption Network (ESAC-Net) indicators [18, 19] measuring the primary and secondary outcomes.

The primary outcome refers to the following index indicator, based on different single ESAC-Net indicators:Percentage of patients with acute non-complicated infections who are treated with antibiotics.

Secondary outcomes refer to the following (ESAC-Net) indicators:2.The use of antibiotics in ambulatory care in defined daily dose (DDD) per 1000 residents (respectively insured persons) per day and region3.Percentage of DDD of broad-spectrum quinolones of all used antibiotics4.Percentage of DDD of broad-spectrum cephalosporins (3rd and 4th generation) of all used antibiotics5.Percentage of patients (18–75 years) with acute bronchitis, patients (> 18 years) with sinusitis, patients (> 2 years) with otitis media and patients (> 1 year) with upper respiratory tract infections/tonsillitis with a prescription of (a) recommended antibiotics, if necessary at all, and (b) less broad-spectrum antibiotics like quinolones6.Percentage of women (> 18 years) with a diagnosis of non-complicated cystitis and a prescription of (a) antibiotics, (b) recommended antibiotics and (c) less broad-spectrum antibiotics like quinolones7.Percentage of patients (18–65 years) with community-acquired pneumonia and a prescription of (a) antibiotics, (b) recommended antibiotics, (c) less broad-spectrum antibiotics like quinolones (> 16 years) and (d) less broad-spectrum antibiotics like cephalosporins or macrolides (> 16 years)8.Percentage of patients with acute non-complicated infections who use medical emergency service9.Percentage of patients with community-acquired pneumonia and hospitalisation

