### Data collection and data management

#### Outcome evaluation

Primary and secondary outcomes, as well as patient characteristics, will be extracted from administrative data at the health insurers involved, so called claims data. This will be done each quarter year. These data provide the basis for the outcome evaluation and the written feedback for participating practices.

Patient characteristics documented from the administrative data include age, sex, years in insurance, insurance status (principal, family or retired member), patient participation in disease management programs (diabetes, breast cancer, asthma, coronary heart disease, COPD, chronic heart failure) and other additional care programs. In addition, prescribing physician identification, medical discipline and physician participation in disease management programs are recorded.

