### Data analysis

#### Outcome evaluation

The primary objective of this study is to examine the change of the antibiotic prescription rate in targeted patients within three intervention arms and the comparison between the three intervention arms. The confirmatory analysis of the primary endpoint will be conducted on the basis of the Intention-To-Treat (ITT) population where all patients will be included in the analysis and assigned to the group they were randomised to.

To account for multiple testing and to assure a global significance level of 5%, a multiple test procedure for hierarchically ordered hypotheses will be applied. In the first stage, differences regarding the primary endpoint (prescription of antibiotics) before and after the intervention in intervention groups B and C are tested. To assure a significance level of 5% within the first level, the hypotheses for the pre- and post comparison will be tested at a local significance level of 5/2%. The second step includes the pre-and post comparison in intervention group A. The significance level of the rejected hypotheses from step one is taken (2.5% if only one hypothesis can be rejected, 5% if both hypotheses can be rejected). If significance is reached in intervention groups A and B, differences between groups A and B will be tested at a local significance level of 5/2%. Similarly, difference between groups A and C will be only tested if significance is reached for groups A and C in the steps 1 and 2. If the hypotheses in step 1 or 2 cannot be rejected, the group comparison will not be tested primarily.

In all stages described above, a logistic mixed effects model will be applied to assess the respective hypotheses regarding the primary endpoint. In the first and second stage, the time (before/after the intervention) is included as fixed effect. A random intercept will be included for patients and for practices. For the comparisons in the third stage, the intervention group will be included as fixed effect additionally. Furthermore, age and gender will be included as covariates. Finally, sensitivity analyses will be conducted using different populations (per protocol population where patients with major protocol violations are excluded and appropriate subgroups). Since all these analyses are based on claims data, missing values cannot be tracked.

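### The confirmatory model adjusts only for age and gender, although chronic-disease programme participation is already extracted and only 14 networks are randomised

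*Protocol article*

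**What the plan says.** All references are to the protocol article.

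- **Primary outcome** (Primary and secondary outcome measures): "Percentage of patients with acute non-complicated infections who are treated with antibiotics".
- **Eligibility** (Patients; Exclusion criteria): patients enter by diagnosis, and "No additional exclusion criteria for participants are defined".
- **Confirmatory model** (Data analysis, Outcome evaluation): a logistic mixed model with random intercepts for patients and practices. Time is a fixed effect, and in the third stage so is intervention group. For patient characteristics: "Furthermore, age and gender will be included as covariates".
- **Data extracted** (Data collection and data management, Outcome evaluation): the list includes "patient participation in disease management programs (diabetes, breast cancer, asthma, coronary heart disease, COPD, chronic heart failure"). The article gives these variables no role in the primary analysis.
- **Randomisation** (Randomisation procedure): 14 networks are split 4, 5 and 5. The allocation is constrained on the number of practices and networks per arm. Patient characteristics are not part of the constraint.
- **Test sequence** (Data analysis): stages one and two compare before with after within an arm. They decide whether A–B and A–C are tested at all.

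**The concern.** Chronic lung disease, heart disease and diabetes plausibly affect whether a patient with an acute infection receives an antibiotic. The article itself hints at this when it says of the guidelines that "they recommend restrained prescription of antibiotics, particularly in healthy patients with acute non-complicated symptoms". If the share of such patients differs between arms, part of an A–B or A–C difference reflects who attended rather than what the programme did. If the share changes between the two periods, the same happens in the pre-post tests, which have no concurrent control. Age and gender will capture some of this, but not all.

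With only 14 allocation units, balance on patient mix cannot be taken for granted, and the Discussion concedes that the small number of units is a possible source of bias. The information needed for a partial safeguard is already being collected.

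**Working it through.** **Inputs from the article** (Sample size calculation; Data analysis): post rates of 50% in A and 45% in B and C; 2.5% two-sided level for A–B; power 80%; correlations of 0.05 (patients in practices) and 0.7 (cases in patients); 80 patients per practice and quarter; 23,933 patients in A and 11,967 in B.

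**Assumed, because the documents give no figure:** a 5-point difference between arms in the share of patients with chronic disease, and a prescribing rate 25 points higher among them.

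**1. Reproduce the plan's sample size.** Two-proportion formula with pooled variance, B half the size of A, pooled rate (0.50 + 0.5 × 0.45)/1.5 = 0.4833:

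n_A = [2.241 × √(0.4833 × 0.5167 × 3) + 0.8416 × √(0.25 + 0.2475/0.5)]² / 0.05² = 2,844

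Design effect: (1 + 79 × 0.05) × (1 + 0.7) = 4.95 × 1.70 = 8.415. The product is 23,932, against 23,933 stated. The factor 1.70 implies two correlated observations per patient; this is inferred from the match and not stated in the article.

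**2. Planned precision of A–B.** √(0.25/2,844 + 0.2475/1,422) = 0.0162, a standard error of about 1.62 points.

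**3. Shift from patient mix, A–B.** Let h be the share with chronic disease in an arm and d the rate difference between patients with and without it. If the programme effect is the same in both groups, the unadjusted arm difference equals the true difference plus (h_A − h_B) × d.

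- 0.05 × 0.25 = 0.0125, or 1.25 points.
- 1.25/5 = 25% of the planned contrast; 1.25/1.62 = 0.77 standard errors.
- A true 5-point difference would appear as 3.75 or 6.25 points, depending on the direction of the imbalance.
- The shift is proportional to both inputs: halving either gives about 0.63 points, doubling either gives 2.5.

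**4. Pre-post tests.** The same formula applies with the change in h between periods. Against the planned falls of 61 − 50 = 11 points in A and 61 − 45 = 16 points in B and C, 1.25 points is 11% and 8%. If falls of that size occur, this is minor; it weighs more if the real falls are small.

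These figures are on the scale of percentage points. The model works on the log-odds scale, so they show the order of size and are not the model's exact bias. They also take the third stage as a comparison of post rates, as the sample size section describes it. A comparison of changes would cancel an imbalance that stays constant over time.

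**The case against.** Four points can be made against this.

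- **The arms are randomised.** On average over allocations the A–B and A–C contrasts are therefore unbiased. That stands, but one allocation of 14 networks is analysed, and the stated random intercepts are for patients and practices, not networks, so a network-level imbalance is not fully reflected in the standard error. Randomisation gives the pre-post tests no protection.
- **Choosing covariates is a matter of judgement, and sensitivity analyses in suitable subgroups are already planned.** This is fair, and naming subgroups is ordinary SAP content. But the article does fix the confirmatory covariates, and it passes over variables it collects.
- **Programme enrolment is not diagnosis.** True: patients with the disease who are not enrolled are missed, so adjustment is partial.
- **The illustration has no anchor in the documents.** Also true, and it is labelled as such.

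A reader might go further and infer that the index counts patients outside its target. The documents do not support this. The same section on exclusions also removes those "who do not fulfil the specific inclusion criteria in each part of the study", and being non-complicated is one of those criteria: "Eligible are patients with a diagnosis of an acute non-complicated infection of the respiratory tract (bronchitis, sinusitis, tonsillitis, otitis media"). How this is coded is not shown; the outcomes "are defined and operationalized based on previous research in Germany". The remark about healthy patients is an emphasis and sets no boundary, and nowhere does the article say that chronic lung or heart disease makes an infection complicated.

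A reader might likewise infer that such patients dilute the effect, with power falling from 80% to about 75%, 70% or 59% at shares of 5%, 10% or 20%. That requires the rates of 61, 50 and 45% to hold only in patients without chronic disease, and no effect in the others. The sample size section gives the rates for the targeted patients without that restriction. If they describe the index as defined, there is no loss against plan.

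**Conclusion.** The point holds as a weakness of the stated model. Age and gender are the only patient covariates, chronic-disease flags are available, few units are randomised without regard to patient mix, and the gatekeeping tests are uncontrolled. Differences in chronic disease between arms or periods can therefore bias the primary comparisons.

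The size is unknown. The 1.25 points in A–B rest on an assumed 5-point imbalance, an assumed 25-point rate difference, an equal programme effect in both patient groups, and no capture by age and gender. If the unseen code definition already removes most patients with chronic disease, the shift would be correspondingly smaller. No conclusion is drawn about an off-target population or about lost power.

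**What to change.** 1. Add participation in the diabetes, asthma, coronary heart disease, COPD and chronic heart failure programmes as covariates in the confirmatory logistic mixed model, at all three stages.
2. Fix each patient's status before the intervention starts (or before the observation period). The data are extracted every quarter, and enrolment after randomisation should not be adjusted for.
3. Among the sensitivity analyses already planned, name one of the primary outcome that leaves out patients with these conditions. Flag them from diagnosis codes in the same claims as well as from enrolment, so that unenrolled patients are also found.

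The confirmatory population stays as it is. No new data are needed, and the change can go into the SAP, which the article says is written before the final analysis. The cost is a few more model terms and a smaller set in the sensitivity analysis.

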### Study procedures

The primary as well as a few secondary outcomes are based on pseudonymized *claims data* (§§ 295, 300 SGB V). Claims data are based on billing data of physicians––like medical prescriptions, diagnoses (ICD-10 codes) and medical service according to the uniform reimbursement scale (‘Einheitlicher Bewertungsmaßstab’) for medical services. Additionally, routine data of statutory health insurance will be used: (a) hospital and ambulatory treatments (as defined by German law §301 SGB V), (b) service of statutory nursing care insurance (as defined by § 105 SGB IX) and (c) basic claims data (‘Stammdaten’, as defined by § 284 SGB V).

The process evaluation is based on surveys and interviews with healthcare providers and stakeholders. Written questionnaires will be given to physicians and, in intervention arm B also to medical assistants, three times during the intervention period. Face-to-face and telephone interviews with physicians, medical assistants and stakeholders will be conducted after the first winter period. The interviews will provide additional insight into perceived impact of intervention components and further explore contextual factors focusing on impact and structures of information exchange in practice networks.

Additionally, focus groups will be used to gain feedback from members of the targeted group at all stages (see Fig. 2) of the planning, implementation and follow-up of ARena interventions and to learn from their experiences and optimise the interventions.

The patient survey will include patients with acute non-complicated infections in participating practices in study arm B. Eligible patients will be identified by their physician (insured by AOK health insurance in Bavaria and diagnosed with an acute non-complicated infection of the respiratory tract, non-complicated cystitis or CAP) and asked to take part in the patient survey by filling in the anonymous questionnaire.

For a detailed recruitment description of study participants, see Additional file 2: Table S2.

#### Financial compensation for study participation

In total, three billing items will be used to reimburse the patient and study-related extra effort. All participating physicians will receive 6€ and medical assistants 5€ per eligible patient and quarter year. Additionally, physicians in intervention group C using the CDSS will receive 2.81€ per eligible patient and quarter year.

Physicians, medical assistants and stakeholders who participate in the interviews within the process evaluation will receive a reimbursement of 50€ each.

### Randomisation procedure

The allocation to the three arms of the study is done by the study statisticians, using a computer program, and concealed from all others in the project. The 14 practice networks are allocated to one of the three intervention arms under the constraints that the arms contain a similar number of practices (not more than one practice difference) based on an estimated participation rate of practices within the networks and that intervention arm A contains 4 practice networks and intervention arms B and C each 5 practice networks. From a total of 34,650 possible allocation outcomes, 112 meet this requirement, from which a computer program randomly picks one.

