**Methods:**

A three-armed cluster randomised trial will be conducted in 14 practice networks in two German federal states (Bavaria and North Rhine-Westphalia) and an added cohort that reflects standard care. The trial is accompanied by a process evaluation.

Each arm will receive a different set of implementation strategies. Arm A receives a standard set, comprising of e-learning on communication with patients and quality circles with data-based feedback for physicians, information campaigns for the public, patient information material and performance-based additional reimbursement. Arm B receives this standard set plus e-learning on communication with patients and quality circles with data-based feedback tailored for non-physician health professionals of the practice team and information material for tablet computers (culture sensitive). Arm C receives the standard set as well as a computerised decision support system and quality circles in local multidisciplinary groups.

The study aims to recruit 193 practices which will provide data on 23,934 patients each year (47,867 patients in total).

The outcome evaluation is based on claims data and refers to established indicators of the European Surveillance of Antimicrobial Consumption Network (ESAC-Net). Primary and secondary outcomes relate to prescribing of antibiotics, which will be analysed in multivariate regression models. The process evaluation is based on interviews with surveys among physicians, non-physician health professionals of the practice team and stakeholders. A patient survey is conducted in one of the study arms. Interview data will be qualitatively analysed using thematic framework analysis. Survey data of physicians, non-physician health professionals of the practice team and patients will use descriptive and exploratory statistics for analysis.

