### Sample size calculation

The sample size calculation is based on the expectation to find an absolute reduction of the antibiotic prescription rate in targeted patients from 61 to 50% in intervention group A and from 61 to 45% in groups B and C. Thus, the effect is expected to be 5% higher in the enriched intervention groups B and C compared to intervention group A.

To control the overall type I error rate at 0.05 (two-sided), a hierarchical 3-step testing procedure will be applied. In the first step, the hypotheses of no difference between the pre- and post prescription rate in group B and C will be tested. If at least one of these hypotheses can be rejected, the hypothesis of no difference in the pre- and post rate in group A will be tested. If, additionally, this hypothesis can be rejected, the hypotheses of no difference between the post rates of groups A and B as well as groups B and C will be tested. The sample size is calculated based on chi-squared tests assuring a (global) power of 80% for the rejection of all the above described, hierarchically ordered hypotheses. Furthermore, to take the clustered structure into account, an intra-cluster correlation coefficient (ICC) for patients in practices of 0.05 and of 0.7 for cases clustered in patients is assumed. Together with the above described expected pre- and post prescription rates in the three groups, this results in a sample size of 23,933 patients in group A, 11,967 patients in group B and 11,967 patients in group C. With an average practice size of 80 patients per quarter this leads to 75 practices in group A, 38 practices in group B and 38 practices in group C.

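### The sample size assumes a 2:1:1 split of practices, the randomisation enforces equal arms, and the abstract implies about 31 patients per practice-quarter where the calculation uses 80

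*Protocol article*

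**What the plan says.** Sample size calculation: the patient numbers are "23,933 patients in group A, 11,967 patients in group B and 11,967 patients in group C". The text continues: "With an average practice size of 80 patients per quarter this leads to 75 practices in group A, 38 practices in group B", with 38 again in group C. The assumed ICCs are 0.05 for patients in practices and 0.7 for cases in patients.

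Randomisation procedure: the 14 networks are allocated so that "the arms contain a similar number of practices (not more than one practice difference", based on an estimated participation rate, and so that "intervention arm A contains 4 practice networks and intervention arms B and C each 5 practice networks".

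Abstract, Methods: the aim is to recruit "193 practices which will provide data on 23,934 patients each year (47,867 patients in total".

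Study population: 193 is also the number of practices taking part at baseline, out of 304 eligible.

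Ambulatory practices and healthcare providers: several specialties may take part, but only "physicians specialised in general practice or internal medicine and functioning as GP will be included in the outcome evaluation".

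**The concern.** The sample size section describes an arm A twice as large as B or C. The randomisation rule makes the three arms equal in practices. A reader cannot tell which arm sizes the trial is meant to reach, or judge later whether recruitment met the plan.

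Practice size is a second conflict. It sets the design effect, so 80 and 31 patients per quarter lead to different required sample sizes. The data period differs as well: one year is implied by the practice counts, two years are stated in the abstract. The number of practices that will actually be analysed is not given.

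**Working it through.** **1. Reproducing the stated arm sizes.** Inputs from the protocol: post-intervention rates of 50% (A) and 45% (B, C), local two-sided alpha 0.025 for the between-arm test, power 80%, ICCs 0.05 and 0.7, 80 patients per practice per quarter. One input is missing and is assumed here: two cases per patient.

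- Design effect = [1 + (80 − 1) × 0.05] × [1 + (2 − 1) × 0.7] = 4.95 × 1.7 = 8.415.
- Two-proportion formula with A:B = 2:1, pooled variance under the null, no continuity correction: pooled rate = (2 × 0.50 + 0.45)/3 = 0.4833.
- n(B) = [2.2414 × √(0.24972 × 1.5) + 0.8416 × √(0.2475 + 0.25/2)]² / 0.05² = 1,422.0.
- Inflated: 1,422.0 × 8.415 = 11,966.2 for B and for C, and 23,932.4 for A. Rounded up, these are the stated 11,967 and 23,933.

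So the published numbers come out of a calculation with a 2:1:1 allocation.

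**2. Practices per arm.** 23,933/(80 × 4) = 74.8, rounded up to 75. 11,967/(80 × 4) = 37.4, rounded up to 38. Total 75 + 38 + 38 = 151. The full patient number is thus taken from four quarters.

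**3. Against the randomisation rule.** Arms may differ by at most one practice; A and B in the calculation differ by 75 − 38 = 37. Equal division gives 64/64/65 of 193, or 50/50/51 of 151. At 193 practices the largest planned arm is 65, ten below the 75 given for A.

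**4. Against the abstract.** The arm sizes add to 47,867, the abstract's total, and half of that is 23,933.5, its yearly figure. Patients per practice-quarter under the possible readings:

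| Reading | Patients per practice-quarter |
|---|---|
| 193 practices, 23,934 a year | 23,934/193/4 = 31.0 |
| 193 practices, all 47,867 in one year | 47,867/193/4 = 62.0 |
| 151 practices, 23,934 a year | 23,934/151/4 = 39.6 |

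None gives 80. Conversely, at 80 per quarter 151 practices yield 151 × 320 = 48,320 in a single year, and 193 practices yield 61,760.

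**5. Equal arms on the same inputs.** With ratio 1:1, n = [2.2414 × √(0.249375 × 2) + 0.8416 × √(0.2475 + 0.25)]² / 0.05² = 1,895 per arm. Times 8.415 this is 15,946 per arm and about 47,840 in total. 15,946/320 = 49.8, or 50 practices per arm.

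**6. Power for A versus B (50% against 45%, alpha 0.025, two cases per patient).** At 31 per quarter the design effect is (1 + 30 × 0.05) × 1.7 = 4.25.

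| Scenario | Design effect | Power |
|---|---|---|
| 2:1:1, 47,867 patients, 80 per quarter | 8.415 | 80.0% |
| Equal arms, 47,867 patients, 80 per quarter | 8.415 | 80.0% |
| 193 practices in equal arms, 23,934 patients, 31 per quarter | 4.25 | 79.6% |
| 75/38/38 practices, 31 per quarter, one year | 4.25 | 68.2% |

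The first two rows agree because the variance of a pairwise comparison is roughly proportional to 1/n(A) + 1/n(B): 2/N + 4/N = 6/N under 2:1:1, and 3/N + 3/N = 6/N under equal arms.

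**The case against.** The best defence is that nothing is lost. Abstract and sample size section agree on 47,867 patients, equal arms with that total keep pairwise power at 80%, and B and C gain what A lacks. The excess of 193 over 151 may be a reserve, or practices outside the outcome evaluation. The balance rule rests on estimated participation, and with 304 eligible practices (about 101 per arm) A might in the end exceed 65. All of this stands, and it rules out any claim that the mismatch alone leaves the trial underpowered. It does not reconcile the text: the rule still aims at equality, and no reading of the abstract returns 80 patients per quarter.

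Three stronger inferences are tempting and are not supported.

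- A reader might take 23,933 as arm A counted twice, once per comparison, and conclude that 3 × 11,967 patients would do. A 2:1 allocation reproduces the figures, whereas a 1:1 calculation gives 15,946 per arm. At design effect 8.415, 11,967 per arm gives only about 67% power per comparison. The smaller total looks sufficient only if the 0.7 ICC is left out.
- A reader might treat the statement that "approximately 40,000 patients with AOK health insurance are registered in 193 participating ambulatory care practices" as proof that 47,867 is impossible. The first is a baseline count, the second a total over two years, and the protocol speaks of both patients and cases, so the two need not conflict.
- A reader might infer that the arms are unbalanced in GP-functioning practices. The protocol does not say how many of the 193 these are, or which practices the balance rule counts, so this is open.

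**Conclusion.** The point holds as an internal contradiction with two parts. The planned arm sizes (75/38/38 practices) are not those the randomisation aims at (about 64/64/65 of 193, or 50/50/51 of 151). The practice size in the calculation (80 per quarter over one year) differs by a factor of about 2.6 from the one the abstract implies (31 per quarter over two years). The number of analysed GP-functioning practices is a further figure needed to settle the matter.

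The consequence is not a demonstrated loss of power. Required arm sizes, practice size, counting unit and data period are simply not fixed by the document. They matter: the stated practice counts at the abstract's practice size for one year would give about 68% for A versus B. The power figures here are per comparison, not the joint power over all hypotheses, and rest on two cases per patient and on the quarterly practice size as cluster size. The contradiction itself needs neither assumption.

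**What to change.** Redo the calculation once, for equal arms, stating:

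- one average practice size, taken from the AOK data;
- the number of GP-functioning practices that enter the outcome evaluation;
- both ICCs (0.05 and 0.7) and the assumed number of cases per patient;
- the counting unit (patients, cases or patient-quarters) and the data period the totals cover.

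Then correct the arm sizes and practice counts in the sample size section, and the practice and patient figures in the abstract, to that one result. If 80 per quarter is confirmed and about 50 GP-functioning practices per arm are available, the answer is about 15,946 patients per arm and the total hardly moves. The cost is then a recalculation and text corrections, with no change to recruitment. If the practice size is nearer 31, the required numbers must be restated accordingly.
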